#### Confidentiality

Each patient who agrees to participate in the protocol will be assigned an identification number that will be used throughout the procedure. This code distinguishes the hospital of origin and the patient’s identification number. All the information collected during the procedure will be confidential (following the data privacy statement found in the informed consent letter) and used only for research purposes and follow-up of adverse effects.

#### Outcomes

The expected primary outcome is clinical improvement, defined as a two-point improvement in the ordinal scale regarding the initial NEWS-2 score. This is an adapted score recommended by the World Health Organization (WHO) and the National Institute for Health and Care Excellence (NICE) to facilitate the early recognition and escalation of deteriorating patients [55, 56]. Although this score is commonly adopted for triage, it can also be used for continuous assessment, particularly in predicting intrahospital mortality. In this context and based on previous experimental data regarding the sustained effect of intranasal dexamethasone, we decided to evaluate the improvement in the initial NEWS-2 score as the first outcome.

The secondary expected outcome includes a reduction in mortality that will be examined during treatment (after randomization), a reduction of the time required for mechanical ventilation, the length of patient’s stay in the hospital, 30-day post-discharge mortality, and intrahospital complications. Viral load, the immune-inflammatory profile, and other physiological parameters will also be evaluated before and after treatment (see above).

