**Methods:**

This is an approved open-label, multicenter, randomized controlled trial to compare the effectiveness of intranasal versus intravenous dexamethasone administered in low doses to moderate and severe COVID-19 adult patients. The protocol is conducted in five health institutions in Mexico City. A total of 120 patients will be randomized into two groups (intravenous vs. intranasal) at a 1:1 ratio. Both groups will be treated with the corresponding dexamethasone scheme for 10 days. The primary outcome of the study will be clinical improvement, defined as a statistically significant reduction in the NEWS-2 score of patients with intranasal versus intravenous dexamethasone administration. The secondary outcome will be the reduction in mortality during hospitalization.

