### Eligibility criteria

Inclusion criteria comprise patients of both sexes (non-pregnant female), aged from 18 to 90 years old, with presumptive SARS-CoV-2 infection and more than 5 days of clinical evolution, with moderate to severe symptoms requiring oxygen support or high flux mechanical ventilation (NEWS-2 ≥ 5), and abnormal CT-chest scan CO-RADS > 3. Patients should be diagnosed with atypical pneumonia, confirmed by chest images and oxygen saturation (SpO_2_) lower than 93% in ambient air or a ratio of the partial pressure of oxygen and the fraction of inspired oxygen (PaO_2_: FiO_2_) equal to or lower than 300 mmHg, and a positive RT- PCR SARS-CoV-2 test. These patients will be allocated into the experimental group or the control group in a 1:1 ratio (two arms) (Fig. 2) according to the randomization.

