#### Sample size and randomization

The analysts of the statistic team calculated the size with EPIDAT version 3.1.2 software, using the option “Sample size and surveillance curves” with an estimated 50% increase in the proportion of patients free of mechanical ventilation [intranasal DXM 70% vs. intravenous DXM 45%]. This value was estimated using the data of the COVID-19 patients registered in Mexican hospitals with a confidence of 95%, power of 80%, and proportion of losses of 10%. A sample size of 60 patients per group was obtained with these parameters. The randomization will be made with Sealed Envelope software. This software is freely available from https://www.sealedenvelope.com/simple-randomiser/v1/lists [Accessed May 5, 2020]. This study is a multicenter randomized controlled trial (Fig. 2).

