#### Statistical analysis

Descriptive statistics using mean (standard deviation) or frequency (percentage) will be used following the dimension scale of the variable. An initial comparison between the hospital will define relevant differences among them. Since healthcare conditions are variable in each hospital included in this study, we will analyze the results with a multilevel mixed longitudinal model. The outcome analysis for NEWS-2 components (i.e., respiration rate, oxygen saturation, systolic blood pressure, pulse rate) will be done using the last observation carried forward (LOCF) in those subjects with at least two observations, this analysis will avoid over-optimistic estimates of efficacy. Other efficacy variables like biochemistry or cell counts will be analyzed without ITT due to the susceptibility to type II error.

Biochemical variables and cell counts will be aggregated using principal component analysis and use the scores if the Kaiser-Meyer-Olkin (KMO) is greater than 0.6 and sphericity *p* < 0.0001. The scores using varimax rotation will be used as dependent variables if the method is suitable for our data. The longitudinal mixed model can be described as:
$$ {y}_{ij}={X}_{ij}\beta +{u}_i+{v}_{j(i)}+{\epsilon}_{ij} $$

where *j* = 1,..,Ti are nested in 10 time points, within *i* = 1,..,5 hospitals. The Xs correspond to fixed variables like the treatments, age, sex, and weight, among other confounders.

A database in vertical format was reshaped to nest the biochemical, inflammatory markers, cell count adjusted by sex, age, and BMI. We will perform restricted maximum likelihood (REML) estimation in case we obtain balanced samples. However, if we obtain an unbalanced sample, we will use maximum likelihood instead [59]. Because we expect a small sample size from some hospitals, we will make inferences using the Kendward-Roger degrees of freedom method. We will make simultaneous inferences about l linear combinations of fixed factors. Despite the complicated situation where *l* > 1 we will consider:
$$ F=\frac{1}{l}{\left(\hat{\beta}-\beta \right)}^T\ L{\left({L}^T\ {\hat{\varphi}}_AL\right)}^{-1}\ {L}^T\ \left(\hat{\beta}-\beta \right) $$

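### The two-point NEWS-2 rule sets no condition on respiratory support, so a patient whose vital signs improve because support was stepped up can count as a responder

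*Protocol article*

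**What the plan says.** The Outcomes section of the protocol article defines the responder: "The expected primary outcome is clinical improvement, defined as a two-point improvement in the ordinal scale regarding the initial NEWS-2 score". The Methods paragraph of the Abstract puts the same outcome as a group contrast, "defined as a statistically significant reduction in the NEWS-2 score of patients with intranasal versus intravenous dexamethasone administration". Neither statement says how a change in respiratory support counts.

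Under Eligibility criteria, patients have "moderate to severe symptoms requiring oxygen support or high flux mechanical ventilation", with a NEWS-2 of at least 5. Every patient therefore starts on some form of support.

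The Statistical analysis section names respiration rate, oxygen saturation, systolic blood pressure and pulse rate as the NEWS-2 components to be analysed, with last observation carried forward. It names neither the level of support nor consciousness.

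Under Sample size and randomization, the trial is sized on the "proportion of patients free of mechanical ventilation [intranasal DXM 70% vs. intravenous DXM 45" (both figures are percentages). Time on ventilation and mortality appear under Outcomes, but only as secondary outcomes.

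**The concern.** A fall in a vital-signs score shows recovery only if support has stayed the same or been reduced. The article itself describes NEWS-2 as a tool for spotting deterioration and prompting escalation. Once support is escalated, the signs that prompted it tend to improve: a ventilator sets or strongly shapes respiratory rate, and saturation follows the oxygen fraction. The two-point rule, followed as written, can then record a worsening patient as a success.

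These scores are observed, not missing, so neither the mixed model nor a missing-data rule corrects them. If the arms differ in how often support is escalated, they also differ in how many such false responders they collect. A true benefit on ventilation would usually be diluted in the primary comparison, and a true harm partly masked there.

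**Working it through.** **1. Can the rule misfire?** The article does not print the scoring bands. I assume the standard NEWS-2 bands, normal temperature, 2 points for being on oxygen (yes or no) and 3 points for sedation.

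| State | RR | SpO2 | SBP | Pulse | Four named components | With oxygen and consciousness |
|---|---|---|---|---|---|---|
| Baseline A, on oxygen | 26 | 91 | 125 | 105 | 3+3+0+1 = 7 | 7+2 = 9 |
| Baseline B, on oxygen | 22 | 93 | 125 | 90 | 2+2+0+0 = 4 | 4+2 = 6 |
| After step to high-flow oxygen | 20 | 96 | 125 | 90 | 0 | 0+2 = 2 |
| After intubation, sedated | 16 | 96 | 115 | 85 | 0 | 0+2+3 = 5 |
| After intubation, sedated, low pressure | 16 | 96 | 95 | 105 | 0+0+2+1 = 3 | 3+2+3 = 8 |

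- Step to high-flow oxygen: A falls 9 to 2 and B falls 6 to 2. Both are successes on the full score, and also on the four components (7 to 0 and 4 to 0).
- Intubation with good pressure: A falls 9 to 5, a success. B falls 6 to 5, which is one point and not a success. On the four components both are successes.
- Intubation with low pressure: on the full score A falls 9 to 8 and B rises 6 to 8, so neither is a success. On the four components A falls 7 to 3, a success, and B falls 4 to 3, not a success.

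The misfire is consistent in these examples for oxygen escalation. For intubation it depends on the baseline and on which items are scored.

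**2. How common is the event?** The complements of the sizing figures are 100 − 45 = 55% and 100 − 70 = 30% ventilated. With 60 per arm that is 33 intravenous and 18 intranasal patients. The article does not say how many would already be ventilated at entry.

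**3. The plan's own figure.** It gives 60 per arm "with a confidence of 95%, power of 80%, and proportion of losses of 10" per cent. The two-sided pooled formula for 0.45 against 0.70, with mean proportion 0.575, is

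n = [1.96√(2 × 0.575 × 0.425) + 0.8416√(0.45 × 0.55 + 0.70 × 0.30)]² / 0.25² = (1.370 + 0.569)² / 0.0625 ≈ 60.2,

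so 61 per arm before losses and 61/0.9 ≈ 68 after them. Sidedness and variant are not stated; a one-sided formula with continuity correction gives 62 after losses. This point does not depend on which was used. I take 60 per arm, and also 60 × 0.9 = 54 analysed.

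**4. Illustration of dilution.** Assume that every ventilation-free patient responds, that all ventilation is new, and that the same share f of ventilated patients in each arm scores a two-point fall. With p the proportion free of ventilation, apparent response is p + (1 − p)f. The difference is

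(0.70 − 0.45)(1 − f) = 0.25(1 − f).

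Power is Φ{[δ√n − 1.96√(2p̄(1 − p̄))] / √(p₁(1 − p₁) + p₂(1 − p₂))}, where p₁ and p₂ are the apparent response rates, p̄ is their mean and δ their difference.

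| f | Intravenous | Intranasal | Difference (points) | Power, 60 per arm | Power, 54 per arm |
|---|---|---|---|---|---|
| 0 | 45.0% | 70.0% | 25.0 | 80% | 75% |
| 0.10 | 50.5% | 73.0% | 22.5 | 72% | 68% |
| 0.25 | 58.75% | 77.5% | 18.75 | 60% | 55% |
| 0.50 | 72.5% | 85.0% | 12.5 | 39% | 35% |

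**The case against.** The strongest reply is that this is a journal article, and that the handling of new ventilation may sit in a full protocol or analysis plan that is not shown. An override may exist there. But the article does state the responder rule, and as stated the rule can classify escalation as success. That goes beyond an omitted detail.

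A reader might infer that nothing offsets the gain from a ventilator. The documents do not support that. The Outcomes section refers to the NEWS-2 score, and the four-item list appears only in the analysis section. If the full score is used, sedation points can cancel the fall, as in the 6-to-5 case.

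A reader might also take the power figures as an estimate. They are not. No document gives f. The 70% and 45% are freedom from ventilation and were never stated as NEWS-2 response rates. Patients ventilated at entry start from an already supported score. If half of the 25-point difference came from such patients coming off the ventilator, f = 0.25 would cost 12.5 × 0.25 ≈ 3.1 points and not 6.25.

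Nor does the design hide harm altogether. Ventilation time, mortality and in-hospital complications are secondary outcomes, and independent experts review safety. What stands is that the primary comparison itself can be misled.

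**Conclusion.** The concern holds in a limited form. As written, the primary outcome can count a patient whose support has been escalated as improved. It is clearest for oxygen escalation and for the four-component analysis, and it is possible but not certain for new intubation. This rests on the wording of the outcome, the entry criteria and the named components. The worked scores also rest on assumed standard bands.

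The plan's own figures make ventilation common and unequal between arms (55% against 30%), so the misclassification could be differential. Its size is unknown. Under the stated assumptions the difference shrinks to 25(1 − f) points, and power at 60 per arm falls from about 80% to 72%, 60% or 39% for f = 0.10, 0.25 or 0.50. With one common f below 1 this calculation shrinks the difference but does not reverse it, so a claim that the result would change sign is not supported.

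**What to change.** Add one sentence to the responder definition. Whatever the NEWS-2, a patient counts as not improved who (a) started mechanical ventilation after randomisation and is still on it, (b) is on a higher level of respiratory support on the assessment day than at baseline, or (c) has died. Death belongs in the rule because last observation carried forward could otherwise keep a favourable score recorded on support.

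Record the level of respiratory support in the case report form, which is already completed daily. Scoring the supplemental-oxygen item alone is not enough: if it is a yes/no item, as assumed here, it does not change when a patient already on oxygen is given more.

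The change affects how patients are classified and not how they are treated. The cost is protocol and analysis-plan wording, one more daily field and a somewhat lower responder rate.

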The internal random structure [$$ {L}^T\ {\hat{\varphi}}_AL $$] can change in different settings, but still will be a good approximation. Simulations studies showed adequate performance of modifications with different REML [60]. Finally, the structure of residual error will be analyzed within the lowest-level group. Once recognized, the covariance structure we will use unstructured, Toeplitz, or exponential corrections. This approach will give unbiased approximation even in presence of unbalanced samples.

The residuals for our mixed models will be considered by the source of present variability: The marginal residuals will predict the marginal errors, the conditional residuals, and the best linear unbiased predictor (BLUP) residuals. The conditional residuals will be standardized with:

$$ {\hat{\varepsilon}}_k^{\ast }=\frac{{\hat{\varepsilon}}_k}{\sigma\ \sqrt{p_{kk}}} $$ , where *p*_*kk*_ represents the *k*th element of the covariance structure. These residuals are functions of the joint leverage of fixed and random effects.

Subgroup analysis will be based on interaction as secondary analysis. This information will help to identify multiplicative effects from basal conditions like the presence of type 2 diabetes, obesity, hypertension, clinical history IECA medication, or other conditions.

All analysis will describe the number of patients with the outcome of interests, the treatment effect (mainly using eta squared), additive and multiplicative interactions with 95% confidence intervals, and the direction of the interaction (positive or negative) by specific subgroups. The analysis will be performed with Stata version 17.0 [StataCorp LLC College Station TX]. A statistical difference with *P* < 0.05 will be considered significant.

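### The Outcomes section puts a two-point cut on NEWS-2 where the abstract has none; used as a responder endpoint, the cut would cost roughly 4 to 15 points of power under a common shift

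*Protocol article*

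**What the plan says.** The article describes the primary NEWS-2 outcome in three ways.

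- Outcomes section: "The expected primary outcome is clinical improvement, defined as a two-point improvement in the ordinal scale regarding the initial NEWS-2 score". Read plainly, this is a threshold that each patient either meets or does not. The same paragraph ends by speaking more loosely of evaluating improvement from the initial score.
- Abstract, Methods paragraph: "defined as a statistically significant reduction in the NEWS-2 score of patients with intranasal versus intravenous dexamethasone administration". There is no threshold here.
- Statistical analysis section: "we will analyze the results with a multilevel mixed longitudinal model", and for the score, "The outcome analysis for NEWS-2 components (i.e., respiration rate, oxygen saturation, systolic blood pressure, pulse rate) will be done using the last observation carried forward". No comparison of responder proportions is named.

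The sample size section uses a different endpoint, "with an estimated 50% increase in the proportion of patients free of mechanical ventilation [intranasal DXM 70% vs. intravenous DXM 45"%], "with a confidence of 95%, power of 80%, and proportion of losses of 10"%, and arrives at 60 per group. No NEWS-2 response rate, standard deviation or effect size appears anywhere in the article.

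**The concern.** NEWS-2 is a multi-point ordinal score. Under a two-point cut, a fall from 12 to 10 counts the same as a fall from 12 to 0, and a gain of one point counts the same as a deterioration of five. The score has to be computed to apply the cut, so the graded information is already in hand when it is thrown away. The Outcomes section cites WHO and NICE for the score as a tool for recognising deterioration; it ties no reason to the two-point threshold.

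With 120 patients there is little power to spare. The question is how much a responder analysis would lose, and whether the article commits the trial to one.

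**Working it through.** **Inputs from the article.** 60 per arm, 1:1 allocation, significance at 0.05 (taken as two-sided), 10% losses, and 45% versus 70% free of mechanical ventilation. **Assumption:** these two rates are borrowed as two-point NEWS-2 response rates, because the article gives none.

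**1. The plan's own figure.** With pooled proportion 0.575, the required n per arm is
[1.960·√(2·0.575·0.425) + 0.842·√(0.45·0.55 + 0.70·0.30)]² / 0.25² = 60.2, so 61 before losses and 61/0.90, so 68, after them. The stated 60 is matched only before losses. If 60 already includes 10% losses, 54 per arm are evaluable.

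**2. Responder comparison.** Power = Φ[(0.25 − 1.960·SE₀)/SE₁].
- n = 60: SE₀ = √(2·0.575·0.425/60) = 0.0903 and SE₁ = √(0.4575/60) = 0.0873. Then (0.25 − 0.1769)/0.0873 = 0.837, so power is 79.9%.
- n = 54: 75.5%.

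**3. Full score, normal latent change.** Shift = probit(0.70) − probit(0.45) = 0.524 + 0.126 = 0.650 SD. Power = Φ(0.650·√(n/2) − 1.960).
- n = 60: Φ(3.561 − 1.960) = 94.5% (94.2% with the t distribution).
- n = 54: 92.2% (91.7% with the t distribution).

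**4. Full score, proportional odds with few categories.** Odds ratio = (0.70/0.30)/(0.45/0.55) = 2.852, log 1.048. Power = Φ(1.048·√V − 1.960), with V = (2n/12)·(1 − Σp̄³) and p̄ the category probabilities averaged over arms.
- Least favourable three-category example, control 0.30/0.25/0.45: the other arm is 0.131/0.169/0.700, Σp̄³ = 0.209, V = 10·0.791 = 7.91. Power is Φ(2.947 − 1.960) = 83.8%.
- A second three-category example gives 87.2%; four to nine categories give 89.0% to 90.7%.

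**5. Simulation.** With integer changes (SD 2 to 4 points) and no deaths, the rank test had about 93% power at 60 per arm, against 80% to 81% for the responder test. With 10% to 20% deaths in each arm ranked worst, it had 88% to 89% against 80% to 81%.

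At 60 per arm the loss is therefore 83.8 − 79.9 = 3.9 points at the low end and 94.5 − 79.9 = 14.6 at the high end.

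**6. Sensitivity to the borrowed rates.** Keeping the 0.650 SD shift but raising control response, responder power at 60 per arm falls to 72% (65% versus 85%) or 63% (75% versus 91%), while full-score power stays at 94%.

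**7. Sensitivity to the shift assumption.** Suppose treatment changes only the share of patients crossing the cut, and the distribution on each side is the same in both arms. Simulated power at 60 per arm is then 81% for the responder test and 66% for the rank test.

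**8. Which full-score analysis.** Assume equal SDs at baseline and end of treatment, correlation r, and the same 0.650 SD shift in change. In units of the final-score SD the shift is 0.650·√(2 − 2r); adjusting for baseline divides this by √(1 − r²). Power at 60 per arm (t distribution):

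| r | Unadjusted final score | Adjusted for baseline |
|---|---|---|
| 0.5 | 94% (shift 0.650) | 98% (0.751) |
| 0.7 | 78% (0.504) | 97% (0.705) |
| 0.8 | 61% (0.411) | 96% (0.685) |

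An unadjusted end-of-treatment score can do worse than the 79.9% of the responder test.

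**The case against.** The strongest reply is that the article never commits to a responder analysis. The abstract has no cut, the planned model is longitudinal, and no test of proportions is named. The sentence beginning "All analysis will describe the number of patients with the outcome of interests" might be taken to support a binary analysis, but it goes on to name eta squared as the main effect measure, which suits a continuous outcome. This stands. A reader might infer that the trial definitely gives up a known amount of power, or that the loss arises whichever definition is kept. The documents support neither: if the abstract's definition is kept, there is no cut and no loss.

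The size is also open to challenge. The 80% power belongs to freedom from ventilation, and both the borrowed rates and the shift are assumptions. This stands too, so the figure can only be given as a conditional range.

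A responder endpoint is a legitimate and readable choice. It can absorb death as failure and discharge as success, whereas a full-score analysis needs explicit rules for both. The reason for two points may also lie in the full protocol, so its absence from the article is not itself a fault. These points bear on how the change is made. They do not remove the threshold from the Outcomes section, which is the only operational definition in Methods and conflicts with the abstract.

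**Conclusion.** The concern holds in conditional form. The Outcomes section sets a two-point cut that the abstract does not contain and the analysis section does not use. If that cut becomes the primary responder endpoint, recorded information is discarded. At 60 per arm, with the 45% and 70% rates borrowed and a common shift assumed, the loss is about 4 to 15 points of power. At 54 evaluable per arm, responder power is 75.5% and full-score power about 80% to 92%. A higher control response would widen the loss; it is plausible, since entry requires NEWS-2 of at least 5 and both arms receive active drug. An effect confined to crossing the cut would reverse it, though the article gives no reason to expect that pattern. The change is worth making because it is cheap and also settles the disagreement over the primary variable. Confidence in the size is moderate at best, since no NEWS-2 input is available.

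**What to change.** Reword the Outcomes section to agree with the abstract:

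- Primary outcome: the full NEWS-2 score, over or at the end of the 10-day treatment period (state which).
- Adjust for baseline NEWS-2 and for hospital. The baseline adjustment is essential, as step 8 of the working shows.
- Rank death as the worst outcome, and state how patients discharged before day 10 are scored.
- Analyse with an ordinal (proportional-odds) or rank-based method, or with the planned mixed model. In each case, say how the death and discharge rules enter the analysis.
- Report the proportion with a two-point improvement in each arm as a supportive result.

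Make the Statistical analysis section name this same variable as primary, so that the analysis of separate components is not mistaken for it.

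The cost is wording in two sections. No added patients or visits are needed, provided the discharge rule does not call for scores after discharge. The small downside is that the main effect measure is less direct than a percentage improved.

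### The abstract and the Outcomes section define the primary outcome in two incompatible ways, and no analysis stated in the article is tied to either

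*Protocol article*

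**What the plan says.** The protocol article describes the primary outcome in three places.

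- Outcomes section, definition: "The expected primary outcome is clinical improvement, defined as a two-point improvement in the ordinal scale regarding the initial NEWS-2 score". No assessment day is attached.
- Outcomes section, end of the same paragraph, with the threshold gone: "we decided to evaluate the improvement in the initial NEWS-2 score as the first outcome".
- Abstract, Methods: "clinical improvement, defined as a statistically significant reduction in the NEWS-2 score of patients with intranasal versus intravenous dexamethasone administration".

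The Statistical analysis section begins with a general intention: "we will analyze the results with a multilevel mixed longitudinal model". The equation that follows is linear, with fixed effects, random effects and an additive error term. NEWS-2 appears in one sentence only: "The outcome analysis for NEWS-2 components (i.e., respiration rate, oxygen saturation, systolic blood pressure, pulse rate) will be done using" last observation carried forward, in subjects with at least two observations. On reporting, the section says "All analysis will describe the number of patients with the outcome of interests" and lists "the treatment effect (mainly using eta squared"). The direction it promises is that of the interactions. The significance threshold is P < 0.05, with no statement of one or two sides.

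The Sample size and randomization section derives 60 per group from a further endpoint, the proportion free of mechanical ventilation (70% versus 45%).

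**The concern.** The two definitions are different kinds of quantity. A two-point improvement from the patient's own starting score is something each patient either achieves or does not, and it leads to a comparison of proportions. The abstract describes a between-arm difference in the score, with no threshold, and makes statistical significance part of the outcome. A single patient cannot be classified under it.

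The two can disagree. If one arm's scores shift without carrying patients across the two-point line, the mean changes and the responder proportion does not. The reverse can also happen.

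The analysis text does not settle the choice. A reader who wanted to know in advance which P value decides this superiority trial could not find out from the article. The trial is open-label, and the Interim analysis section allows it to end if no trend is seen, without naming the efficacy outcome. That makes the open choice more consequential.

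**Working it through.** **1. The passages side by side**

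| Place | Quantity | Level | Two-point threshold |
|---|---|---|---|
| Abstract, Methods | Significant reduction in NEWS-2, intranasal versus intravenous | Group, test result | No |
| Outcomes, definition | Improvement from initial NEWS-2 | Patient | Yes |
| Outcomes, restatement | Improvement in the initial score | Not stated | No |
| Statistical analysis | Four NEWS-2 components | Component | No |
| Sample size | Free of mechanical ventilation | Patient | Not a NEWS-2 endpoint |

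Neither the total NEWS-2 score nor two-point responder status is named as a dependent variable in the Statistical analysis section. The linear model could take a total score. It is not suited to a yes/no responder outcome. Eta squared is a share of variance, so it has no sign and no unit.

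**2. The plan's own figure**

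Inputs from the Sample size section: 70% versus 45%, 95% confidence, 80% power, 10% losses. Two-sided, pooled variance, no continuity correction, mean proportion 0.575:

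n = [1.960 × √(2 × 0.575 × 0.425) + 0.842 × √(0.70 × 0.30 + 0.45 × 0.55)]² / 0.25²
= [1.370 + 0.569]² / 0.0625 = 60.2, so 61 per group before losses, and 61 / 0.9 = 67.8, so 68 after.

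One-sided with continuity correction gives 55, and 62 after losses. The stated 60 is thus reproduced to within 2, either two-sided before losses or one-sided after them. In both cases it is a calculation for ventilation, and it supports neither NEWS-2 definition.

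**3. Illustration of multiplicity**

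If each of the four listed components were tested at 0.05, the tests were independent, and any one sufficed: 1 − 0.95⁴ = 0.185. Positive correlation between the vital signs would lower this.

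**4. Power if a NEWS-2 responder endpoint is adopted**

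The article gives no NEWS-2 responder rate, so the control rate is an assumption, taken as 30–60%. Evaluable patients: 60 × 0.9 = 54 per arm; two-sided 0.05.

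Power = Φ{[d√n − 1.960 √(2p̄(1−p̄))] / √(p₁(1−p₁) + p₂(1−p₂))}

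Example, 55% versus 30%: d√n = 0.25 × √54 = 1.837; numerator 1.837 − 1.370 = 0.467; denominator 0.676; Φ(0.690) = 0.755.

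| Difference | Power over control rates 30–60% |
|---|---|
| 25 points | about 75–84% |
| 20 points | about 55–62% |
| 15 points | about 34–38% |

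**The case against.** The best defence is that this is a journal article, that a statistical analysis plan may exist, and that such a plan would name the primary model. That is a fair answer to missing detail. It does not answer two definitions that conflict in the text shown, because an analysis plan cannot settle which of them the protocol meant.

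Four stronger readings are tempting, and the documents do not carry them.

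- A reader might infer that the primary outcome is never tested. The general mixed model for the results could be fitted to a repeated total score, and the promised counts of patients with the outcome fit a responder analysis. What stands is that no stated analysis is linked to either definition.
- A reader might infer four separate component tests. The sentence on components mainly sets a missing-data rule. It does not say whether each component gets its own model, or whether values are carried forward before scoring. The 18.5% therefore stays an illustration.
- A reader might object that supplemental oxygen is missing from the component list. The article nowhere sets out the full NEWS-2 items, so this cannot be shown from it.
- A reader might say that the report could not show which arm did better. Counts of patients with the outcome, if given by arm, would show that. The criticism applies to eta squared itself as the main effect measure.

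**Conclusion.** The concern holds in this form: the article gives two incompatible definitions of its primary outcome and ties no stated analysis to either. A responder comparison, a comparison of scores and comparisons of components are all compatible with the text, and each could be presented as the primary result at P < 0.05. This has to be corrected before any confirmatory claim.

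The finding is textual and rests on no numerical assumption. No single error rate can be attached, because the article does not fix a procedure; 18.5% is a ceiling for one unstated procedure. The power consequence is also conditional. With 54 evaluable per arm, a NEWS-2 responder endpoint comes near the planned 80% only for a difference of about 25 percentage points, and falls to about 55–62% at 20 points, given control rates of 30–60%.

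**What to change.** Use one definition in the abstract, the Outcomes section and the Statistical analysis section. For example: the proportion of all randomised patients whose total NEWS-2 at the end of treatment (day 10) is at least two points below the pre-treatment value.

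- Count death before day 10 as no improvement, and state in advance how discharge before day 10 is scored. The Procedures section closes the case report form at the end of treatment or at death, so patients who die earlier will have no day-10 score.
- Test the endpoint once, two-sided at 0.05, adjusted for hospital and baseline NEWS-2. Report the risk difference with its 95% CI in place of eta squared.
- Make the mean score over time and the component vital signs secondary.
- Remove the requirement of statistical significance from the abstract's definition of the outcome.
- State that 60 per group was calculated for freedom from mechanical ventilation, and give the power for the chosen NEWS-2 endpoint with its assumed control rate.

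The cost is mainly rewording. The article describes daily data collection but does not name NEWS-2 among the daily items, so the sponsor should confirm that the total score is available at day 10, and what is available after early discharge. The sponsor gives up the choice among definitions, and the restated power may be less favourable.
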